#### Sample Size

To estimate the appropriate sample size, we used data from a previous study showing statistically significant differences between the PSDs of EEG recordings from tinnitus and nontinnitus participants [53]. The averaged power in the theta band was approximately 15.6 and 14.3 µV^2^ for the tinnitus and nontinnitus subjects, respectively, and the pooled SD was 0.5 µV^2^. A power analysis to test a two-sided hypothesis at a significance level of.05 and a power of 80% was estimated to require a sample size of 39 participants in each group. Up to 50 participants in each group meeting the eligibility criteria after pre-enrollment and the screening session will be recruited.

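### The sample size of 39 per group does not follow from the printed means and SD, which give about 4 per group

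*Protocol article*

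**What the plan says.** The whole calculation is in Methods, Sample Size, of the protocol article. It draws on a previous EEG study comparing people with and without tinnitus and gives these inputs:

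- Group means: "The averaged power in the theta band was approximately 15.6 and 14.3 µV^2^ for the tinnitus and nontinnitus subjects", respectively.
- Spread: "the pooled SD was 0.5 µV^2".
- Test: "A power analysis to test a two-sided hypothesis at a significance level of.05", with 80% power.
- Result: "was estimated to require a sample size of 39 participants in each group".
- Recruitment ceiling: "Up to 50 participants in each group meeting the eligibility criteria".

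The section names no dropout rate, multiplicity adjustment, within-subject correlation, smaller target difference or other test.

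**The concern.** A difference of 1.3 µV² against an SD of 0.5 µV² is 2.6 standard deviations. Two groups that far apart can be told apart with a handful of participants each, so a requirement of 39 per group cannot come from these inputs.

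This statement is the article's only justification for the study's size, and the two ways of reading it lead to very different conclusions. If the SD of 0.5 is right, 39 per group is about ten times what the stated target needs, and the power for that contrast is essentially 100% instead of 80%. If 39 is right, the assumed effect was about 0.64 SD and the printed inputs overstate it fourfold. A reader interpreting a null between-group result (secondary objectives 2 and 3) would not know what difference the study was built to detect. Anyone reusing the printed inputs would plan a far too small study if the SD is the wrong figure.

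**Working it through.** **Inputs, all from the Sample Size section.** Difference 15.6 − 14.3 = 1.3 µV²; SD 0.5 µV²; two-sided alpha 0.05; power 0.80; equal groups.

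**Step 1: try to reproduce 39.**

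Standardised difference: d = 1.3/0.5 = 2.6.

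Normal approximation: n per group = 2(1.960 + 0.842)²/d² = 2 × 7.849/6.76 = 2.32, so 3.

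Exact two-sample t-test (noncentral t, df = 2n − 2, noncentrality d√(n/2)):

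| n per group | Power at d = 2.6 |
|---|---|
| 3 | 0.668 |
| 4 | 0.863 |
| 5 | 0.948 |
| 39 | essentially 1 |

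The requirement is 4 per group (3.59 before rounding up). The stated 39 is not reproduced.

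**Step 2: look for a reading that rescues 39.** Exact t-test, 80% power and two-sided unless stated:

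| Variant | n per group |
|---|---|
| Rounding: difference 1.2 to 1.4, SD 0.45 to 0.55 | 3 to 5 |
| One-sided test | 3 |
| 90% power | 5 |
| 99% power | 7 |
| 0.5 read as a variance (SD = √0.5 = 0.707) | 6 |
| Bonferroni, 5 tests | 6 |
| Bonferroni, 1000 tests | 12 |

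None comes near 39. Attrition cannot explain it either: going from 39 to 50 would allow for 1 − 39/50 = 22% loss, but that step starts from 39.

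**Step 3: solve backwards from the stated size.** At 80% power and two-sided .05:

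- 39 per group: d = 0.643. With the 1.3 µV² difference, SD = 1.3/0.643 = 2.02 µV². With the printed SD, the difference is 0.643 × 0.5 = 0.32 µV².
- 50 per group: d = 0.566.

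An SD of exactly 2.0 µV² gives d = 1.3/2.0 = 0.65 and n = 38.1, which rounds up to 39.

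**Step 4: a possible origin, as an assumption only.** If 0.5 were a standard error, the SD would be 0.5√m, where m is the group size in the source study. The article does not give m. Values of 15, 16 and 17 give SDs of 1.94, 2.00 and 2.06 and requirements of 36, 39 and 41 per group; m = 10 gives 25 and m = 20 gives 48. So 39 fits m = 16, but nothing in the article confirms it.

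**The case against.** The mismatch itself is hard to dispute. The best case on the other side concerns what may be concluded from it.

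First, all three printed figures could be accurate quotations if the authors sized the study on a smaller target difference, about 0.32 µV² with SD 0.5, and left it out. This stands as a possibility: the check shows that 39 does not follow from the printed inputs, not which figure is false. The section would still be wrong as written, because it presents the printed figures as the basis for 39.

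Second, the near-100% power applies only to a between-group contrast in theta power with SD 0.5. The primary hypothesis under Objectives is a within-subject comparison of baseline and poststimulus, and Statistical Analysis plans a mixed model for it. This stands too. The power statement says nothing about the primary comparison, and nothing here shows that the study as a whole is oversized.

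Third, the error may be harmless: this is an observational study, enrolment started in February 2018, and 39 to 50 per group is ample if the SD is 0.5. That comfort depends on the very figure in doubt. If the SD is about 2.0, the printed effect is four times too large.

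Nor does the article's condensed form help. The figures are printed and do not agree, and fuller detail elsewhere would not make them agree.

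**Conclusion.** The concern holds. With the inputs as printed, the requirement is 4 per group by exact t-test (3 by normal approximation), against 39 stated. At 39 per group those inputs give essentially 100% power for the between-group theta contrast, not 80%. The stated size corresponds to a standardised difference of about 0.64, roughly a quarter of the printed 2.6.

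This rests on a plain two-sample comparison of means with equal groups, the only design that the section's inputs describe. It does not depend on rounding of those inputs. Which figure needs correcting cannot be settled from the article. Because the power statement is the sole basis given for the study's size, it should be corrected.

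**What to change.** Return to the source data and reconcile the difference, the SD and the number per group in the Sample Size section:

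- **If the SD is about 2.0 µV²** (for instance because 0.5 was a standard error), print that SD and the standardised difference it implies, about 0.64 to 0.65.
- **If 0.5 µV² is the SD**, say that 39 per group was not derived from the 1.3 µV² difference. Give the target difference actually used, or the differences detectable with 80% power: 0.64 SD (0.32 µV²) at 39 per group and 0.57 SD (0.566 × 0.5 = 0.28 µV²) at 50.

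In either case, name the test and say that the calculation concerns the between-group theta contrast. The cost is one corrected sentence, with no change to enrolment or conduct.

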#### Recruitment

Participants will be recruited through the outpatient clinic and tinnitus consultation at our department. In addition, advertisements will be displayed in public areas and posted on the Web. No staff members from the clinic with a dependency relationship will be recruited. Potential participants who have the willingness and ability to perform all tests required for the study will sign and date an informed consent form before the start of the study procedure.

### Study Procedure

Table 1 provides an overview of the study procedure. During pre-enrollment, a checklist will be filled by potential study participants to assess the tinnitus-associated psychological status (tinnitus subjects only), general health conditions, neurological conditions, and medical history. Potential study participants will then be invited to the screening session to assess the study eligibility. The total duration of the screening session will be 70 minutes for tinnitus subjects and 35 minutes for nontinnitus subjects. Eligible subjects will be invited to the assessment session with a total duration of 150 minutes, including preparation and postassessment cleaning time. The assessment consists of 2 subsessions with 30 minutes each, separated by a 10-minute break. All participants will be asked to avoid the consumption of coffee 5 hours before the assessment session [54].

### Data Collection

#### Infrastructure and Measurement Equipment

All study-specific measurements will be performed in an acoustic chamber (6 m × 4 m × 2 m) certified for clinical audiometry with a broadband reverberation time of approximately 200 ms. The chamber is air-conditioned and provides electromagnetic shielding. For extended audiometry, tinnitometry, and RI assessment, we will use a custom-written script (The MathWorks Inc, v.2017b) with the Psychophysics- Toolbox extensions [55]. Acoustic stimuli will be presented through an external ASIO sound card (Scarlett2i2, FocusRite) and high-definition insert earphones (Triple-Driver, 1MORE Inc). Calibration of the acoustic stimuli (ie, pure tone and third-octave noise) will be confirmed using a head and torso simulator, including 2 ear simulators (Type 4128, Brüel & Kjaer) and an audio analyzer (UPV Audio analyzer DC-250 kHz, Rohde & Schwarz).

**Table 1 table1:** Overview of the study procedure.

Item	Pre-enrollment	Screening session	Assessment session
Medical History	✓	N/A^a^	N/A
Questionnaires (over the Web)	✓	N/A	N/A
Audiometry	N/A	✓	N/A
Tinnitometry	N/A	✓	N/A
Residual Inhibition	N/A	✓	✓
Electroencephalography	N/A	N/A	✓

^a^N/A: not applicable.

#### Medical History and Questionnaires

The medical history contains information about the patients’ health status and the cause of their tinnitus such as the presence of cardiovascular diseases, tinnitus objectivity, signs of otorrhea, and other external or middle ear diseases and drugs that can directly influence the analysis. The following questionnaires will be administered to assess the effects of tinnitus, co- occurring complaints, and health-related quality of life: (1) a general health checklist, aimed at identifying health problems that could affect the brain activity of interest; (2) the Tinnitus Handicap Inventory [56] to assess the severity of tinnitus symptoms; and (3) Hospital Anxiety and Depression Scale [52] to assess depression and anxiety.

#### Audiometry

Standard pure tone audiometry will be performed to assess bone conduction hearing thresholds (in dB hearing level) at 0.5, 0.75, 1, 2, 3, 4, and 6 kHz and air conduction hearing thresholds (in dB hearing level) at 0.125, 0.25, 0.5, 1, 2, 3, 4, 6, and 8 kHz. In addition, an extended assessment of air conduction hearing thresholds (in dB SPL) will be performed at 9, 10, 11, 12, and 13 kHz using a custom-written script and insert earphones.

#### Tinnitometry

Subjects will classify the laterality (ie, unilateral left, unilateral right, bilateral “at both ears,” or central “in the head”) and quality (ie, tonal or noise like) of their tinnitus. The tinnitus pitch will be matched with either pure tone or third-octave noise stimuli ranging from 0.125 to 13 kHz, and the tinnitus loudness at tinnitus pitch (in dB SPL) will be estimated. The MML corresponds to the level of a third-octave noise stimulus (in dB SPL) at which it just renders tinnitus unperceivable. The LDL (in dB SPL) corresponds to the level at which subjects report the stimulus to be uncomfortably loud will be measured.

#### Residual Inhibition

For both ears, the air conduction thresholds for third-octave noise stimuli will be obtained for a stimulus centered at the tinnitus pitch and a 0.5-kHz control frequency. At the tinnitus pitch, the level of the RI stimulus will be specified by adding 20 dB to the MML [57] of the tinnitus ear (in the unilateral case) and by adding 20 dB to the MML of each ear separately (in bilateral or central cases). In the unilateral case, the contralateral ear will be presented with a stimulus level that is specified by adding the RI stimulation sensation level (the difference between the RI stimulus level and the third-octave noise hearing threshold) of the tinnitus ear to its third-octave noise hearing threshold. The third-octave noise control stimulus centered at 0.5 kHz will be presented at the same sensation level as the RI stimulus.

To assess the RI capability, the following procedure will be followed using a 60-second RI stimulus presented through insert earphones. For each of 10 presentations, participants with tinnitus will indicate whether they experience partial or complete suppression of their tinnitus by rating the loudness change on a Likert scale (−5 to +5) immediately after the stimulus presentation. In addition, to obtain time course of their tinnitus change, tinnitus subjects will be asked to continuously rate the loudness change on the Likert scale until their tinnitus has returned to the loudness before the RI stimulus.

#### Electroencephalography

EEG recording will be performed with an active electrode 64-channel biopotential measurement system (ActiveTwo, Biosemi). After selection of a suitable EEG head cap and adjustment of the cap position, electrode gel (Signa Gel, Parker Laboratories, Inc) will be injected, and the electrodes will be attached. The position of the electrodes was selected according to the 10/20 standard scheme for 64 electrodes and 2 additional channels for the active common mode sense and passive-driven right leg electrodes. In addition, the three-dimensional coordinates of all electrodes will be recorded. For electrooculography (EOG) and electromyography (EMG) recording, 8 adhesive surface electrodes will be placed at the head of subjects (left and right outer canthus, right infraorbital and supraorbital, left and right masseter, and left and right mastoid). The offset of each electrode will be checked, measured, and, if required, electrode gel will be added until the offset falls within ±40 mV. Participants will be instructed to use a response box for an automated recording procedure (MATLAB script). Trigger events, such as measurement start, stimulus onsets or offsets, and participants’ responses, will directly recorded by the EEG software (ActiView, Biosemi).

EEGs will be recorded during 2 blocks consisting of 12 trials each (Figure 1). Each trial consists of 4 epochs—“Baseline,” “Stimulus,” “Poststimulus,” and “Feedback.” The “Baseline” epoch lasts 40 seconds in which spontaneous resting-state EEG is recorded. During the “Stimulus” epoch, the RI and control stimuli will be presented to subjects through the insert earphones for 60 seconds. The RI and control stimuli are played in a randomized sequence to avoid habituation of neural responses.

**Figure 1 figure1:**
[figure not shown]
Overview of the electroencephalography recording procedure. RI: residual inhibition.

Subjects are blinded with respect to the order of the stimulation sequence. In the “Poststimulus” epoch, spontaneous resting-state EEG will be recorded for 40 seconds. Tinnitus subjects will be asked to indicate the return of their tinnitus to the normal loudness level by a button press and stay with minimal movement until the end of this epoch. Non-tinnitus controls will be asked to press a button immediately after they perceived a narrow-band stimulus with a central frequency and sensation level same as their matched tinnitus subjects. The stimulus has a duration of 3 seconds and will start 37 seconds after turning off the RI or control stimuli. This process will minimize bias by performing a similar task as tinnitus subjects. In the “Feedback” epoch, EEG recording will be stopped, and participants will be asked to rate the degree of tinnitus loudness change immediately after the stimulus presentation, as well as the change of psychological condition on a scale from −5 to 5 (−5 indicating quieter or feeling less burdened, 0 indicating no change, and +5 indicating louder or feeling more burdened) using the response box. The duration of this epoch is approximately 10 seconds.

Several steps will be taken to suppress or reduce artifacts during EEG recording. The acoustic chamber is electromagnetically shielded. The measurement amplifier is connected by a fiber optic data transfer to the measurement computer outside of the chamber. Before EEG recording is started, light and all power lines will be switched off and no electrical devices, except the battery-powered EEG amplifier, will be active inside the chamber In addition, the chamber will be air-conditioned to avoid contact artifacts of electrodes caused by sweating. During the assessment, participants will be asked to sit relaxed with their eyes closed; they will be instructed to move their body or eyes as little as possible to minimize motion artifacts, especially when making a button press response. To account for muscle and eye artifacts, EOG or EMG are additionally recorded.

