As tinnitus often originates from peripheral and central auditory mechanisms [13,14], the assessment of abnormal neural activity may be a potential approach for objective diagnosis. A number of research groups have suggested that tinnitus is accompanied by changes in the brain [15-20] and can be examined using electroencephalography/magnetoencephalography (EEG/MEG) [17,19,21-27]. In particular, spontaneous brain oscillations, that is, the ongoing brain activity in the absence of external events, have been intensively investigated using EEG/MEG. Traditional EEG/MEG power bands of resting-state activity have been quantified between people with tinnitus and controls [17,22]. One theory explaining group differences in the EEG/MEG power within specific frequency bands focuses on the thalamocortical dysrhythmia model. This model predicts an increase of power in low frequencies (delta and theta bands) and high frequencies (gamma band) in the auditory cortex in subjects with tinnitus [18]. Furthermore, marked alterations of EEG/MEG oscillations across other brain regions and power bands have been reported in the prefrontal cortex [28-31], cingulate cortex [29-38], parahippocampus [15,26,31,34,36,37,39-42], and insula [26,37,43], implying the involvement of other brain areas and power bands. Nevertheless, poor matching of gender, age, and hearing loss status across groups, as well as other confounding factors, hinder the interpretation of study findings and generate inconsistencies [44]. To minimize variance across subjects, a within-subject measurement comparing the brain activity during a baseline period (tinnitus with abnormal brain activity) with a period after the suppression of tinnitus (stabilization of abnormal activity) may overcome this limitation.

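### Drowsiness and time on task are only partly handled in the eyes-closed EEG; the between-group comparisons (secondary objectives 2 and 3) are the ones left exposed

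*Protocol article*

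**What the plan says.** **Recording conditions.** Under Electroencephalography, "participants will be asked to sit relaxed with their eyes closed" and, before recording starts, "light and all power lines will be switched off". Study Procedure adds: "All participants will be asked to avoid the consumption of coffee 5 hours before the assessment session".

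**Timing.** "The assessment consists of 2 subsessions with 30 minutes each, separated by a 10-minute break" (Study Procedure). "EEGs will be recorded during 2 blocks consisting of 12 trials each" (Electroencephalography). Each trial has a Baseline epoch of 40 s, a Stimulus epoch of 60 s, a Poststimulus epoch of 40 s and a Feedback epoch of about 10 s with EEG stopped.

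**Order.** "The RI and control stimuli are played in a randomized sequence to avoid habituation of neural responses".

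**Tasks.** In the Poststimulus epoch, tinnitus subjects press a button when their tinnitus is back to its normal loudness. Controls press a button to a 3-s sound that starts 37 s after the stimulus ends. Ratings follow every trial.

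**Cleaning and model.** Data Preprocessing removes independent components judged artifactual by inspection and by comparison with EOG and EMG. Statistical Analysis lists group, time-point (baseline, stimulus, poststimulus) and stimulus type as fixed effects, and subject as the random effect. Time-point is the epoch within a trial, not time into the session.

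**Outcome.** The Objectives section refers to traditional EEG power bands in general. The Introduction ties the leading theory to delta, theta and gamma, and Sample Size uses theta.

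**The concern.** Sitting still in the dark with eyes closed for most of an hour, after a coffee restriction, invites drowsiness. I take it as general EEG knowledge, not stated in the document, that drowsiness raises delta and theta power. Theta is the planning band, and both bands belong to the theory under test.

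Drowsy EEG is genuine brain signal, so removing eye and muscle components leaves it in. With no block or trial term, any trend over 24 trials goes into the residual. If one group is sleepier than the other, the difference appears as a group difference in power and would be read as tinnitus-related. Secondary objectives 2 and 3 compare the groups at baseline and at poststimulus directly, without a within-subject reference.

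**Working it through.** **1. Timing (epoch lengths from Electroencephalography).**
- One trial: 40 + 60 + 40 + 10 = 150 s. Twelve trials: 1,800 s = 30 min, which reproduces the stated subsession length. Two blocks: 60 min of task.
- Rest EEG: 24 × (40 + 40) s = 32 min. Sound: 24 × 60 s = 24 min. Rating with EEG stopped: 24 × 10 s = 4 min. EEG runs for 56 min.

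**2. Linear drift and the primary contrast.** Let power drift by D over the session (size assumed). The Baseline midpoint is 20 s into a trial and the Poststimulus midpoint 120 s, so they lie 100 s apart.
- One drift over 60 min: 100/3,600 = 2.8% of D.
- A drift of D in each 30-min block, reset by the break: 100/1,800 = 5.6% of D.
- For D = 0.5, 1.3 and 2.6 µV² the bias is 0.014–0.028, 0.036–0.072 and 0.072–0.144 µV².
- The 100-s gap is the same in RI and control trials, so the bias cancels in (poststimulus minus baseline) RI minus control.

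This does not cover non-linear change within a trial, such as arousal by the sound followed by relaxation. The 0.5 kHz control stimulus addresses that only in part.

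**3. Drift that differs between groups (objectives 2 and 3).** Trial k (k = 0 to 23) starts at 150k s, and the mean of k is 11.5.
- Mean Baseline position: (150 × 11.5 + 20)/3,600 = 0.485 of the session.
- Mean Poststimulus position: (150 × 11.5 + 120)/3,600 = 0.5125.
- The yardstick is the planning difference in Sample Size: 15.6 − 14.3 = 1.3 µV².

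| Group difference in drift (assumed) | Baseline bias | Share of 1.3 | Poststimulus bias |
|---|---|---|---|
| 0.5 µV² | 0.24 µV² | 19% | 0.26 µV² |
| 1 µV² | 0.48 µV² | 37% | 0.51 µV² |
| 2 µV² | 0.97 µV² | 75% | 1.03 µV² |

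**4. What randomized order does.** Assume 6 RI and 6 control trials per block; the article gives no ratio. The SD of the difference in mean position, for one subject in one block, is √(13/3) = 2.08 trials, or 2.08 × 2.5 = 5.2 min. Over two blocks it is 2.08/√2 = 1.47 trials. Averaged over 39 subjects it is 1.47/√39 = 0.24 trials, about 35 s. This is noise with mean zero: randomization balances order but does not stop habituation or drift.

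**5. What block and trial terms can do.** Every subject in both groups has the same 2 × 12 trial positions. These terms are therefore unrelated to group. They take drift out of the residual but leave the average group difference essentially where it was.

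**The case against.** The strongest reply is that this is a condensed article. Segment-rejection rules, vigilance scoring and order covariates commonly sit in a full protocol or analysis plan, and their absence alone would be no finding. That is right, and it keeps the point moderate. But the article does set out its recording conditions, its cleaning steps and its model terms, and the point is about what those do as stated.

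The second reply is that the design already guards against time on task. There is a baseline inside every trial, randomized order, a control stimulus, a button-press task in both groups, a rating after every trial and a break. This stands for slow drift in the primary contrast, as step 2 shows.

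The third reply is that both groups have the same timing and coffee restriction, that controls are given a task meant to resemble the tinnitus group's, and that nothing in the document shows a difference in alertness. This also stands as far as it goes. The tasks still differ, since one group monitors its own percept and the other waits for an external tone. Audiogram matching does not equalize alertness.

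**Conclusion.** The point holds in a limited form. As written, the cleaning leaves drowsy EEG in the outcome and the listed model leaves drift in the residual. The main exposure is in secondary objectives 2 and 3, and only if the groups differ in alertness. Its size is unknown: the 19% to 75% rests on assumed group differences in drift of 0.5 to 2 µV², linear over the session.

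Stronger readings that a reader might infer are not supported:
- *An hour of eyes-closed rest with no safeguards.* Rest EEG is 32 minutes, and several features give partial protection.
- *Drowsiness could produce the primary result.* Slow linear drift contributes 2.8% to 5.6% of its size to that contrast and nothing to RI minus control.
- *The hypothesis is about delta and theta only.* It covers the traditional bands in general.
- *A modest imbalance in drowsy seconds reproduces the planned effect.* The planning difference is 1.3/14.3 = 9.1%. An imbalance of 9 to 18 percentage points would match it only if a drowsy second carried 50% to 100% more theta, which the document does not give. The 9.1% is also a between-group figure and no measure for the within-subject contrast.

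**What to change.** 1. **Model.** Add block and trial number within block as fixed effects, with trial-level values as the unit. State that this is for precision and does not remove between-group vigilance bias.
2. **Drowsy segments.** Fix one rule based on slow eye movements in the EOG already recorded (outer-canthus electrodes are listed). Apply it identically to both groups and all epochs, masked to group and epoch. Use it at least as a sensitivity analysis for objectives 2 and 3, and report the excluded share by group and epoch. Do not use responses to the 3-s probe: it exists only in controls and only at 37–40 s of Poststimulus, so it would create unequal exclusion by group and epoch.
3. **Wording.** Say that the randomized sequence balances order, instead of that it avoids habituation.

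The cost is two model terms, one masked pass over existing recordings and somewhat fewer segments per subject. No new data are needed. Because the abstract says that analysis is under way, the report should state when the rule was fixed.
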